### Recruitment {20}

We will recruit participants at the study centers in Hamburg, Düsseldorf, and Würzburg. They are either patients who seek psychosocial support through the study centers’ psycho-oncology clinics or patients who are referred to the study. Under the supervision of a licensed psychotherapist or senior physician, experienced trained study personnel will initially screen patients for inclusion criteria via in-person assessment. Trained study personnel with at least advanced psychotherapeutic training will conduct a comprehensive recruitment interview and hand out written standardized patient information on both treatment arms. After obtaining written informed consent, included patients will complete the baseline assessment including self-report measures and a diagnostic interview. Subsequently, included patients will be randomized.

Study personnel will contact patients’ family caregivers via telephone for participation upon patients’ consent. Study personnel will give comprehensive study information and if family caregivers verbally consent to participate, they will be sent written informed consent and study information via mail. In the event of a patient’s death, participating family caregivers will receive another questionnaire 3 months after the patient’s death (post-death survey). Follow-up for deceased patients will be performed until 1 year after inclusion of the last participant.

Diagnostic interviews will be conducted via telephone or face-to-face by trained advanced psychology or medical students; self-report questionnaires and follow-up assessments will be sent via mail. We will document the number of excluded participants as well as reasons for exclusion. For non-responder analyses, we will collect basic demographic and medical data from non-participants upon their consent.

## Assignment of interventions: randomization

### Sequence generation: who will generate the sequence {21a}

The randomization sequence is generated using statistical computing software R, version 4.5.2 [96], and sealed in consecutively numbered envelopes by a person independent of the study personnel.

#### Sequence generation: type of randomization {21b}

Block randomization with an allocation ratio of 1:1 is carried out using electronically generated numbers. Blocks of variable length are used to generate the sequence in order to avoid predictability of allocation. Randomization is stratified by center.

### Allocation concealment mechanism {22}

Study personnel do not have access to the randomization list (concealed allocation sequence). After the included patients provided written informed consent and completed baseline assessment (diagnostic interview, self-report questionnaire), the independent person randomly assigned them to ORPHYS or TAU by opening the envelope and informing a therapist from the respective intervention group.

### Implementation {23}

The therapist then contacts the patient and arranges the session dates. Treatment allocation is communicated either during this conversation or in a separate contact after completion of T0 assessments.

## Assignment of interventions: blinding

### Who will be blinded {24a}

Since this is a psychotherapy study with two active intervention groups, blinding of participants and therapists is not possible. Recruitment interviews and assessments (diagnostic interviews, mailing of self-report questionnaires) are conducted only by trained, clinically experienced research assistants, who have no knowledge of patients’ treatment allocation.

### How will blinding be achieved {24b}

Before each assessment, participants are reminded to not disclose their treatment allocation to study personnel. Study personnel not involved in data collection will perform statistical analysis. Statistical support is provided by the Department of Medical Biometry and Epidemiology at the University Medical Center Hamburg-Eppendorf (SL).

### Procedure for unblinding if needed {24c}

N/a, trial is non-blinded.

## Data collection and management

### Plans for assessment and collection of outcomes {25a}

Figure 1 shows the data collection process. After enrollment in the study, participants complete the baseline assessment (diagnostic interview, self-report questionnaire) within 14 days and are randomized afterwards. Post-randomization assessments are collected at fixed intervals (3, 6, 9, and 12 months after baseline assessment). The primary outcome demoralization is measured at baseline, 3, 6, 9, and 12 months after baseline. Based on an expected treatment duration of 24 sessions and a 30% session cancellation rate, we expect treatment to last about 8 months. Taking into account the range of treatment duration from 15 to 31 sessions, we expect completion of treatment after 5 to 11 months. Medical information including end-of-life care will be collected via medical chart review (electronic patient file, medical reports). We will conduct two semi-structured interviews with participating family caregivers at 6 and 12 months. Table S1 shows the planned assessments and corresponding time points.

**Fig. 1 Fig1:**
[figure not shown]
Data collection process

### Plans to promote participant retention and complete follow-up {25b}

Each ORPHYS and TAU session will be documented on a structured, standardized form including date and time of the session, setting (e.g., face-to-face, telephone, home visit), attendance, occurrence and severity of adverse events, and study or treatment dropout. If patients miss an appointment without canceling in advance, therapists will contact them via phone and document reasons for cancellation and the next planned appointment. If participants do not return the self-report questionnaires within 14 days, study personnel will remind them via telephone.

We document information relevant to the data collection process (e.g., dates of follow-up assessments, return of self-report questionnaires, dropout). If participants discontinue or deviate from intervention protocols, study personnel will document reasons for study or treatment dropout. Outcome data that are collected before dropout will be included in the analyses.

### Data management {26}

We document participants’ personal data (name, contact data), corresponding study IDs, and information relevant to the data collection process (e.g., date of follow-up assessments, return of self-report questionnaires, dropout) in Microsoft Access (LTSC 2021). Throughout the data collection process, participants’ study IDs are used (pseudonymization). After completion of the RCT, the study ID list will be deleted. The Microsoft Access file and the audio recordings of the therapy sessions are stored on encrypted flash drives, which are kept in locked cabinets and backed up once a month. Only senior study personnel have access to the Microsoft Access file and the audio files.

Diagnostic interview sheets and self-report questionnaires are stored in locked cabinets. Research assistants will enter the data of the assessments into IBM SPSS Statistics, Version 29 [97]. The SPSS file is stored on secured servers with regular backup, which can only be accessed by the study personnel. To ensure data quality, 20% of the manually-entered data in Microsoft Access and SPSS will be entered twice and range checks for data values will be performed in SPSS. Inconsistencies will be resolved by checking the original data in the questionnaires.

### Confidentiality {33}

Data will be handled in line with the respective Federal Data Protection Acts. All staff will be required to undergo data management training and sign a data protection commitment document. Data integrity will be monitored closely. Study personnel will undergo Good Clinical Practice training prior to study initiation. Collected data will be archived for 10 years after completion of the study. The data security concept was confirmed with the local data protection officers of each study center.

## Statistical methods

### Statistical methods for primary and secondary outcomes {27a}

To investigate the treatment effect for the primary outcome demoralization at post-intervention, we will calculate a linear mixed model using the difference between post-intervention and baseline scores (change-from-baseline model). The model will include intervention (ORPHYS vs. TAU), time point and the interaction intervention group X time point as fixed effects to test group differences and a random intercept to account for inter-individual differences. The model will include trial site, therapists and patients as nested random effects. We will conduct a confirmatory analysis of the between-group contrast at the 6-month follow-up.

We will investigate treatment effects for the continuous secondary outcomes (death anxiety, dignity-related distress, quality of life) at post-intervention accordingly. To investigate the treatment effect for the binary outcomes (mental disorders) at post-intervention, we will calculate a mixed-effects logistic regression model with intervention (ORPHYS vs. TAU), time point and the interaction intervention group X timepoint as fixed effects as well as trial site, therapists and patients as nested random effects.

Analyses will be performed two-sided with alpha = 0.05. There will be no adjustment for multiple testing. While analysis of the primary outcome will be confirmatory, all other analyses will be exploratory, and specified *p*-values for these analyses should be interpreted descriptively. All analyses will be performed using IBM SPSS Statistics 29 [97] and R, version 4.5.2 [96].

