##### Primary outcome

We assess demoralization using the Demoralization Scale-II (DS-II), a 16-item self-report questionnaire measuring feelings of hopelessness and helplessness as well as loss of meaning and purpose [37, 43]. Items are scored on a 3-point Likert-scale from 0 (never) to 2 (often), with a total score ranging from 0 to 32 (Cronbach’s alpha = 0.93) [44]. Higher scores indicate higher demoralization.

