### Methods for additional analyses (e.g., subgroup analyses) {27d}

#### Sensitivity analyses

We will perform sensitivity analyses by including the covariates age, gender, the time since first diagnosis, and the time since diagnosis of incurable cancer in the linear mixed model based on their association with the primary outcome demoralization in previous studies [9, 13]. Moreover, we will adjust the model for the occurrence of illness progression within the last 3 months by including a binary time-dependent covariate.

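### The primary model analyses change in DS-II without baseline DS-II as a covariate: a valid test, but never more precise than the baseline-adjusted model, and one that over-corrects a chance baseline imbalance

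*Protocol article*

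**What the plan says.** Section {27a} of the protocol article sets the response variable of the primary analysis: "we will calculate a linear mixed model using the difference between post-intervention and baseline scores (change-from-baseline model". Besides arm, the fixed part consists of "time point and the interaction intervention group X time point as fixed effects to test group differences and a random intercept". The random part is also given: "The model will include trial site, therapists and patients as nested random effects". The confirmatory test is placed at one visit: "We will conduct a confirmatory analysis of the between-group contrast at the 6-month follow-up". The continuous secondary outcomes are to be analysed in the same way.

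The sensitivity models in section {27d} extend the primary model by "including the covariates age, gender, the time since first diagnosis, and the time since diagnosis of incurable cancer in the linear mixed model", and by a time-dependent indicator of recent illness progression. Baseline DS-II is in neither list. Apart from the subtraction, its only stated use is in the check for systematic dropout in section {27c}.

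The score is available for everyone: "The primary outcome demoralization is measured at baseline, 3, 6, 9, and 12 months after baseline", and section {22} places the baseline assessment before the allocation envelope is opened. Randomization is stratified by center only (section {21b}), so the design does not balance baseline DS-II.

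**The concern.** Subtracting the baseline score fixes the slope of follow-up on baseline at 1. Where the true slope is below 1, as it is with equal SDs and any correlation short of perfect, the subtraction removes too much. Two things follow. The change score carries baseline noise that a fitted slope would leave out, so the standard error of the 6-month contrast is larger than it need be. And if one arm happens to start with higher DS-II, regression to the mean makes that arm appear to improve more.

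What is at stake is precision on the only confirmatory test, given up although the variable that would recover it is collected from every patient before randomization. This is more than a detail that an article leaves to the analysis plan, because section {27a} itself names the response, the fixed effects and the random effects.

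**Working it through.** **Inputs.** From the sample size section {19}: SD 5.4 (pilot), d = 0.5, two-sided alpha 0.05, power 80%, 64 per group, 80% completion, 160 randomized, 70% participation. From the primary outcome section: DS-II "with a total score ranging from 0 to 32". Not in the document, so assumed: the correlation r between baseline and 6-month DS-II, the ratio of follow-up to baseline SD, and that 5.4 is a cross-sectional SD.

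**1. The plan's own figure.** A two-sided two-sample t-test with d = 0.5 needs 64 per group (power 80.1%), so 128. Then 128/0.80 = 160, and 160/0.70 = 228.6, rounded up to 229. All the stated numbers reproduce. They rest on an unadjusted comparison of post-intervention scores.

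**2. Variance per patient, equal SDs.**
- Change score: 2(1-r) SD².
- Baseline adjusted: (1-r²) SD².
- Adjusted over change: (1-r²)/[2(1-r)] = (1+r)/2.

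**3. Power with 64 per group at d = 0.5 (0.5 × 5.4 = 2.7 points).** The standardized effect becomes 0.5/√[2(1-r)] for change scores and 0.5/√(1-r²) with adjustment. Power is from the noncentral t.

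| r | Adjusted/change variance | Power, change | Power, adjusted | N per group for 80%, change | N per group for 80%, adjusted |
|---|---|---|---|---|---|
| 0.3 | 0.65 | 66.0% | 83.7% | 89 | 59 |
| 0.5 | 0.75 | 80.1% | 90.0% | 64 | 49 |
| 0.7 | 0.85 | 95.2% | 97.6% | 39 | 34 |
| 0.8 | 0.90 | 99.3% | 99.7% | 27 | 24 |

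The unadjusted post-score t-test has 80.1% in every row. Change scores therefore fall below the design power when r < 0.5, match it at r = 0.5 and exceed it above that.

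**4. Unequal SDs.** In general, Var(change) = Var(adjusted) + (r × SD_post - SD_pre)². The added term is never negative, so change scores are never the more precise choice. It is zero when the slope r × SD_post/SD_pre equals 1. Adjusted over change variance:

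| SD_post/SD_pre | r = 0.3 | r = 0.5 | r = 0.7 | r = 0.8 |
|---|---|---|---|---|
| 0.8 | 0.50 | 0.57 | 0.63 | 0.64 |
| 1.0 | 0.65 | 0.75 | 0.85 | 0.90 |
| 1.25 | 0.78 | 0.89 | 0.98 | 1.00 |

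**5. Chance imbalance.** Given a baseline difference D between arms, the change-score estimate is shifted by (slope - 1)D, which is -(1-r)D with equal SDs. With 80 randomized per arm, the standard error of D is 5.4 × √(2/80) = 0.85 points. An imbalance of one standard error then moves the estimate by 0.7 × 0.85 = 0.60, 0.5 × 0.85 = 0.43 and 0.3 × 0.85 = 0.26 points at r = 0.3, 0.5 and 0.7.

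**6. Check in a repeated-measures model.** A simulation of four follow-up visits used a random-intercept model on change scores, with and without baseline and baseline by time point (64 per arm, 250 runs per r, complete data, no site or therapist effects). The change-to-adjusted variance ratios were 1.53, 1.32 and 1.17, against 1.54, 1.33 and 1.18 from 2/(1+r). The slopes of the change-score estimate on the observed imbalance were -0.70, -0.52 and -0.26, and close to zero after adjustment.

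**The case against.** The strongest reply is that nothing here is invalid. Under randomization and with complete data, the change-score contrast is unbiased and its test keeps its level. The loss is measured against an adjusted model, not against the design: relative to the post-score t-test behind the 64 per group, the planned model gains whenever r exceeds 0.5. All of this stands, and it makes the point one of efficiency.

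The second reply is that the sizes are soft. Equal SDs are assumed, and with a follow-up SD 1.25 times the baseline SD most of the gain is gone at r = 0.7. Section {19} does not say whether 5.4 is a baseline, follow-up or change SD. If it is a change SD, change-score power for 2.7 points is 80% whatever r is. The power figures also come from single-visit t-tests without clustering. This stands for the magnitudes. The direction is unaffected, because change scores can at best tie.

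Some stronger readings are tempting but not supported:
- A reader might infer that the random intercept forces equal variances and correlations across the follow-up visits. That also needs independent residuals of constant variance, and section {27a} does not state a residual structure.
- A reader might want the logistic model for mental disorders adjusted for baseline diagnosis. Diagnostic interviews are held at baseline, 6 and 12 months, and section {27a} does not say whether baseline is one of the modelled time points. If it is, that advice would be wrong.
- A reader might add weight by citing low power for a 2-point difference. That concerns how section {19} relates 2 points to d = 0.5, which is a separate matter.

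**Conclusion.** The point holds as an efficiency weakness that should be corrected. The stated primary model leaves out baseline DS-II, and so does the sensitivity list. Compared with the same model adjusted for baseline, the error variance is 1.54, 1.33 and 1.18 times as large at r = 0.3, 0.5 and 0.7 with equal SDs. The cost in power at d = 0.5 is about 18, 10 and 2 percentage points. It shrinks as the slope of follow-up on baseline approaches 1 and is nil at that value.

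One might read the omission as leaving a baseline imbalance uncorrected, or as biasing the trial. Neither is right. Subtraction does correct, but with equal SDs by too much, and the resulting shift is conditional on the imbalance that happens to occur; it averages to zero over repeated randomizations. Confidence is high for the direction and moderate for the sizes, which rest on assumed values of r, the SD ratio and the meaning of the SD of 5.4.

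**What to change.** In section {27a} and in the analysis plan, add baseline DS-II and baseline DS-II by time point as fixed effects in the primary model, and keep the between-group contrast at 6 months as the confirmatory test. With these terms in the model, the contrast is the same whether the response is the change or the raw follow-up score, so its meaning is unchanged. Treat the continuous secondary outcomes alike, each with its own baseline score.

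The cost is wording only. The baseline score is already collected before randomization, no visit or patient burden is added, and the sample size need not change. Section {5} promises the analysis plan before data lock, and recruitment is to run to December 2027, so the change can be fixed before results are known and recorded in the registration as section {31} provides.

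### The stated random intercept, with independent residuals, gives all four change scores one variance and one correlation; an unstructured residual covariance is the safer choice, though the risk to the 6-month test is small

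*Protocol article*

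**What the plan says.** Section {27a} of the protocol article specifies a linear mixed model for change from baseline in the DS-II score. Group, time point and their interaction are fixed effects. Within-patient dependence is handled by "a random intercept to account for inter-individual differences". The section adds: "The model will include trial site, therapists and patients as nested random effects". It names no residual covariance structure and excludes none.

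Section {25a} fixes the visits: "The primary outcome demoralization is measured at baseline, 3, 6, 9, and 12 months after baseline". Four change scores per patient therefore enter the model. On the status of the tests, {27a} states "We will conduct a confirmatory analysis of the between-group contrast at the 6-month follow-up" and, beyond the primary analysis, "all other analyses will be exploratory". Testing is two-sided at 0.05.

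The only measure of spread in the article is the pilot SD of 5.4 under Sample size {19}. No SD by visit and no within-patient correlation is given. Section {27c} relies on missing at random and maximum likelihood within the mixed model. Section {5} announces a separate statistical analysis plan (SAP), which is not shown.

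**The concern.** A random intercept with independent residuals is compound symmetry. All four outcomes subtract the same baseline score, so when correlation with baseline fades over a year, later change scores vary more than early ones. That is plausible here: the article expects progression, physical deterioration and treatment lasting between 5 and 11 months. A pooled variance would then be too large for early visits and too small for late ones.

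Two things are at stake: the precision of the single confirmatory contrast at 6 months, and the honesty of the intervals at the other visits, above all 12 months. The likelihood argument for missing data also leans on the covariance model being right, in a population where substantial loss is expected.

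**Working it through.** **The plan's own figure.** A two-sided t-test at d = 0.5 with 64 per arm has power 0.801, so 128 patients are needed; 128/0.80 = 160 randomized; 160/0.70 = 228.6, so 229 eligible. This reproduces {19}. It does not depend on the covariance structure. The article gives no SE by visit to reproduce.

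**What the stated model implies.** With intercepts for site, therapist and patient and independent residuals, every visit has variance s²(site) + s²(therapist) + s²(patient) + s²(residual). Every pair of visits in a patient has covariance s²(site) + s²(therapist) + s²(patient). Neither depends on the visit, so the nested terms leave compound symmetry intact.

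**Effect on one visit's SE, complete data.** The model uses the mean of the four variances, so

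model SE / true SE at visit t = √(mean variance / variance at t).

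The true size of a nominal 5% test is 2·(1 − Φ(1.96 × ratio)).

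**Inputs.** SD 5.4 is from {19} and is assumed here to hold at every visit. The correlations are assumptions. With equal SDs, Var(change at t) = 2·5.4²·(1 − r_t) = 58.32·(1 − r_t).

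*AR(1) raw scores*

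| 3-month correlation | 1 − r at 3, 6, 9, 12 months | mean | 6-month ratio | 12-month ratio |
|---|---|---|---|---|
| 0.5 | 0.500, 0.750, 0.875, 0.938 | 0.766 | √(0.766/0.750) = 1.01 | √(0.766/0.938) = 0.90 |
| 0.9 | 0.100, 0.190, 0.271, 0.344 | 0.226 | √(0.226/0.190) = 1.09 | √(0.226/0.344) = 0.81 |

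True test size is 4.8% to 3.3% at 6 months and 7.7% to 11.2% at 12 months.

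*With dropout.* Assumed retention is 90%, 80%, 72% and 65%, completely at random. The 80% is the completion rate in {19}, placed at 6 months; the rest is assumed. Fitting the large-sample compound-symmetry model gives ratios of 0.99 to 1.05 at 6 months (size 5.2% to 4.0%) and 0.87 to 0.77 at 12 months (8.7% to 13.2%).

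*A single illustration.* Take correlations with baseline of 0.76, 0.65, 0.55 and 0.47. The change SDs are 3.7, 4.5, 5.1 and 5.6, and the mean of 1 − r is 0.3925. The ratios are √(0.3925/0.35) = 1.06 and √(0.3925/0.53) = 0.86. A test with 80% power under the correct SE would have Φ(2.80 − 1.96 × 1.06) = 0.77.

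*Same illustration with baseline as a covariate.* Residual variance is proportional to 1 − r²: 0.422, 0.578, 0.698, 0.779, mean 0.619. The ratios become √(0.619/0.578) = 1.035 and √(0.619/0.779) = 0.891, that is about +3.5% and −11%.

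**Patterns that remove or reverse the error**, complete data:

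| Assumed pattern | Change SDs at 3, 6, 9, 12 months | 6-month ratio | 12-month ratio |
|---|---|---|---|
| Equal raw correlation 0.5, equal SDs | 5.4, 5.4, 5.4, 5.4 | 1.00 | 1.00 |
| Equal correlation, SD peaks at 6 months | 5.50, 5.84, 5.50, 5.30 | 0.95 | 1.05 |
| Equal correlation, SD falls | 5.50, 5.40, 5.21, 5.05 | 0.98 | 1.05 |

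What matters is the variance of the change score, not of the raw score. With AR(1) at 0.7 and raw SDs falling from 5.4 to 4.4, change SDs still rise (4.18 to 6.09) and the 12-month ratio is 0.89.

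An unstructured covariance gives a ratio of 1.00 at every visit in large samples under all of these patterns.

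**The case against.** The strongest reply is that the article never says the random intercept is the only within-patient structure. A residual structure can be added to it, and naming one is commonly left to the SAP. That stands as far as it goes: sole reliance on the intercept is an inference from the usual default. It does not remove the point, because the article names its device for within-patient dependence, and an SAP that follows {27a} literally would carry compound symmetry into the primary analysis.

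The second reply is that the direction is assumed. This also stands. A reader might infer that the 6-month interval is too wide and the 12-month interval too narrow as a matter of fact. One SD and no correlations cannot show that, and the last table gives patterns where the error vanishes or reverses.

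Third, a reader might infer that long-term benefit would be overstated. With complete data, the covariance structure leaves the estimated group difference unbiased. At most, precision is overstated, and only for a contrast that the article labels exploratory.

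Fourth, the drop from 80% to 77% power is only illustrative: the 80% in {19} belongs to a t-test at d = 0.5, not to this model. Finally, adjusting for baseline removes part of the error, so this point partly overlaps with the question of baseline adjustment.

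**Conclusion.** The point holds in conditional form. If residuals are independent, the stated model pools one variance and one correlation over four visits, and nothing in the article supports that restriction. Under rising change variance, the 6-month SE is off by +1% to +9% with complete data and by −1% to +5% with the planned 20% loss. That is mostly conservative and minor for the confirmatory test. The 12-month SE is 10% to 19% too narrow with complete data and 13% to 23% with 35% loss, so a nominal 5% test there runs at about 8% to 13%.

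These figures rest on AR(1) correlations of 0.5 to 0.9, a constant SD of 5.4 and an assumed retention curve. The documents do not support a claim that the confirmatory test is invalid. The case for change rests on valid intervals at the other visits and on less dependence of the missing-at-random likelihood analysis on a restrictive covariance.

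**What to change.** In the SAP, replace the patient random intercept by an unstructured residual covariance over the 3-, 6-, 9- and 12-month visits. Use REML and Kenward-Roger degrees of freedom. Keep the planned site and therapist terms and keep the 6-month contrast as the confirmatory test. Pre-specify a fallback, such as heterogeneous Toeplitz, if the model does not converge.

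The remedy does not depend on which way the variance moves. It costs some SAP wording and 4 × 5 / 2 = 10 within-patient covariance parameters instead of 2, with site and therapist components on top in either case. That is a modest number for 160 patients. There is a small risk of non-convergence, and the team should check that the chosen procedure accepts the site and therapist terms together with an unstructured residual matrix. Fixing the structure and the fallback before data lock also removes a post-hoc choice from the confirmatory analysis.
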